### Outcomes

The primary outcome of the study is ICU mortality. The secondary outcomes include the following: a) 28-day all-cause mortality; b) improvement in SOFA scores; c) improvement in the Japanese Association for Acute Medicine (JAAM) and International Society on Thrombosis and Hemostasis (ISTH) scores; and d) bleeding risks during the study period. The daily bleeding monitor sheet is shown in Table 2.

**Table 2 Tab2:** Daily bleeding monitor sheet

Classification	Manifestation	Intervention
Major bleeding	- Intracranial bleeding - Gastrointestinal hemorrhage (haematemesis, tarry stool) - Severe nose bleeding - Other fatal bleeding	Stop infusion of study drugs and recorded in the CRF
Minor bleeding	- Mild gum bleeding - Mild epistaxis - Airway mucosa bleeding - Puncture site bleeding - Bruise or skin purpura	Attending physicians monitor and make a decision

*CRF*, case report format

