### Criteria for exiting or suspending the trial

Infusion is to be stopped if there is major or life-threatening bleeding, such as intracranial bleeding, gastrointestinal hemorrhage, or severe nosebleeds. If there are some signs of mild bleeding, such as coffee-like stomach contents, mild gum, or skin mucosa bleeding, the physician should closely monitor and judge according to the actual situation.Infusion was suspended 2 h before major surgery and resumed 12 h after the surgery.If the patient at high risk for thrombosis events, such as venous thromboembolism or acute myocardial infarction, must be treated with anticoagulation therapy, the trial needs to be stopped.If there is an unexplained decline of 50% or greater in platelet counts, especially onset between day 5 and 10 after treatment, or the patient meets the 4Ts scoring system for heparin-induced thrombocytopenia (HIT) diagnosis [22], or a positive test of platelet serotonin-release assay (SRA)

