## Discussion

The trial is a multicenter, randomized, double-blinded RCT. We hypothesize that UFH will reduce ICU mortality compared with placebo in sepsis-induced DIC and has no obvious impact on bleeding.

The implication of anticoagulation and antithrombotic therapies for sepsis has drawn increasing attention during the last few years [23, 24]. Coagulation abnormalities are quite common in the early stage of sepsis. Endothelial injury, the formation of microthrombi, and excessive inflammatory factors act mutually and contribute to organ dysfunction or even death during sepsis [25]. However, some anticoagulants that only inhibit microthrombosis or replenish the loss of intrinsic anticoagulant factors have been proven to not improve organ function or reverse mortality in sepsis or septic shock [26]. Of note, the large RCTs on rhAPC allowed the use of heparin for preventing deep venous thrombosis and showed a survival benefit in the subgroups treated with heparin relative to the groups who did not receive heparin [9]. Intriguingly, the re-analysis of the three trials (the PROWESS using rhAPC [9], KyberSept using AT [10], OPTIMIST using rTFPI [27]) demonstrated that in the control group, the use of heparin can independently reduce 28-day mortality relative to the patients without heparin [28]. Furthermore, a single-center prospective randomized double-blind study (HETRASE) demonstrated that UFH had no beneficial effect on the survival of sepsis patients, although there was no increased risk of bleeding. However, the participants enrolled in the HETRASE study suffered from less severe sepsis with APAHCEII<10 and were more heterogeneous in the population [21].

In the trial, we enrolled participants with more rigorous criteria. The modified criteria, including platelet counts, prothrombin time, and D-dimer, are applied to diagnose DIC in septic patients. We exclude fibrinogen in the modified DIC criteria. The characteristics of DIC differ according to the underlying disease [23]. For trauma-induced DIC, excess fibrinolysis exists to counter massive thrombotic events, which shows decreased levels of fibrinogen [29]. In sepsis, coagulation activation occurs with injured fibrinolysis [23]. The imbalance of coagulation and fibrinolysis results in massive clot formation. Therefore, the level of fibrinogen is normal or even elevated in sepsis-induced DIC patients.

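### The stopping criteria and the Table 2 bleeding sheet define major bleeding differently, so a survived major bleed at an unlisted site fits neither row of the sheet

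*Protocol article*

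**What the plan says.** Three parts of the protocol article bear on this.

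- **Criteria for exiting or suspending the trial.** The infusion stops for a class of bleeding introduced by examples: "Infusion is to be stopped if there is major or life-threatening bleeding, such as intracranial bleeding, gastrointestinal hemorrhage, or severe nosebleeds". A milder class is left to the physician's judgement: "If there are some signs of mild bleeding, such as coffee-like stomach contents, mild gum, or skin mucosa bleeding".
- **Outcomes, Table 2 (daily bleeding monitor sheet).** The major row holds intracranial bleeding, "Gastrointestinal hemorrhage (haematemesis, tarry stool"), severe nose bleeding and "Other fatal bleeding". The action for that row is "Stop infusion of study drugs and recorded in the CRF". The minor row holds mild gum bleeding, mild epistaxis and "Airway mucosa bleeding - Puncture site bleeding - Bruise or skin purpura", with no residual entry.
- **Where the outcome is named.** The Abstract gives the frequency of major haemorrhage as a secondary outcome. The Outcomes section lists bleeding risks over the study period and refers the reader straight to Table 2. The Discussion states the hypothesis that heparin "has no obvious impact on bleeding".

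**The concern.** Bleeding is the main safety question for heparin in patients selected for abnormal coagulation, and the Discussion names major haemorrhage as one of its two main concerns about the drug. Twenty centres will classify bleeding from what is written. If the sheet has no place for some major bleeds, sites must force them into a row, code them differently from one another, or leave them off. Major bleeds left off the sheet lower the count of major haemorrhage. When heparin truly raises bleeding, that shrinks the absolute difference between arms and so leans towards the trial's own hypothesis of no apparent effect on bleeding.

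**Working it through.** The article gives no bleeding rate and no figure for this outcome, so there is nothing to reproduce. The check is a comparison of the two sections.

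| Event | Stopping criteria | Table 2 |
|---|---|---|
| Intracranial bleeding | Stop | Major |
| Gastrointestinal haemorrhage | Stop | Major, with haematemesis and tarry stool in brackets |
| Severe nosebleed | Stop | Major |
| Fatal bleed, other site | Within the open class | Major (residual entry) |
| Survived major bleed, other site (e.g. retroperitoneal, thoracic, surgical-site) | Within the open class | **No row** |
| Coffee-like stomach contents | Mild | **No row** |
| Mild gum or skin bleeding | Mild | Minor |

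**Step 1, residual class.** The two sections agree on the three named major sites. For every other site the stopping criteria ask whether the bleed is major or threatens life, while Table 2 asks whether it is fatal. The second class is strictly narrower. What lies between them cannot fall into the minor row, because that row is a closed list of specific, mostly superficial signs.

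**Step 2, is the gap foreseeable?** Yes. The stopping criteria provide for suspending the infusion around major surgery and resuming it afterwards, so surgical patients are expected and surgical-site bleeding is possible. Fatality is also hard to apply on a daily sheet whose action is to stop an infusion, because it may be known only later.

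**Step 3, a related weakness.** Airway and puncture-site bleeding sit in the minor row with no severity limit. A severe but survived bleed at those sites would be coded minor, which also lowers the major count.

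**Step 4, direction of the effect.** Let p0 and p1 be the true major-bleeding risks in the control and heparin arms, and let c be the share that the sheet captures, assumed equal in both arms. The counted difference is c × (p1 − p0), which is smaller than the true one. The counted ratio is (c × p1)/(c × p0) = p1/p0, which is unchanged. So equal under-capture reduces the absolute difference and the power, but not the risk ratio.

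**Step 5, illustration only.** All rates and capture shares below are assumptions. Power is for 300 per arm at two-sided 0.05.

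| Assumed true risks | Difference, c = 1 | Difference, c = 0.7 | Power, c = 1 | Power, c = 0.7 |
|---|---|---|---|---|
| 2% v 5% | 3.0 points | 2.1 points | 52% | 38% |
| 3% v 8% | 5.0 points | 3.5 points | 77% | 61% |
| 5% v 10% | 5.0 points | 3.5 points | 64% | 49% |

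For 3% v 8%, the expected counts fall from 9 v 24 (300 × 0.03, 300 × 0.08) to 6.3 v 16.8 (each × 0.7). Nothing in the article says whether c is near 1 or well below it.

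**The case against.** The strongest reply is that Table 2 is a monitoring sheet, and the article never calls it the outcome definition. The Outcomes section speaks of bleeding risks in general. The section on risks and adverse events has AEs and SAEs recorded for 28 days and reported to the data and safety monitoring board, and the data-collection section has transfusion products recorded daily. A survived retroperitoneal bleed should therefore appear somewhere. This stands. It makes the under-count conditional on counting from the sheet, and it means that harm is not lost altogether. It does not remove the mismatch, since Table 2 is the only classification of bleeding printed with the outcome.

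Three stronger readings are tempting and are not supported.

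- A reader might infer that the two sections contradict each other on gastrointestinal bleeding. The stopping criteria themselves separate gastrointestinal haemorrhage from coffee-like contents, and the bracket in Table 2 can be read as limiting the major item to haematemesis and tarry stool. Read that way, the sign is merely missing from the minor list, which does not change a count of major bleeds.
- A reader might infer from the Data analysis section that a risk difference with confidence interval is planned for mortality alone. The section specifies one for ICU mortality but does not rule out others, and the effect measure for a secondary safety outcome may properly sit in an analysis plan that is not shown.
- A reader might take the power figures as the size of the problem. They rest wholly on assumed rates and capture shares. The power at full capture reflects sample size and owes nothing to the wording.

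**Conclusion.** The point holds as a mismatch of definitions. The stopping criteria cover any major or life-threatening bleed, whereas the residual major entry in Table 2 covers only fatal ones and the minor list is closed. A survived major bleed at an unlisted site has no row. It would be missing from the major-haemorrhage outcome if that outcome is taken from the sheet as written, although AE/SAE recording should still register it. The absent row for coffee-like stomach contents is a lesser omission.

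The conclusion rests on two assumptions: that the word fatal is applied literally, and that the sheet feeds the outcome. It may be loose wording for life-threatening, but then it still needs correcting. The size of any under-count cannot be derived from the document. Only its direction can be stated: a lower major-bleed count and, where heparin raises bleeding and capture is equal in both arms, a smaller absolute difference.

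**What to change.** 1. The investigators should reconcile the stopping criteria with Table 2, including where coffee-like stomach contents belong. Because the major row of Table 2 also triggers an action on the infusion, changing it changes clinical management. Which bleeding stops treatment is for the clinicians to settle.
2. Separate the outcome from that action. For outcome counting only, adopt one written definition of major bleeding that includes non-fatal major bleeding at any site, with stated severity criteria.
3. Classify events against that definition blind to allocation, using the AE/SAE records together with the blood counts and daily transfusion volumes already collected.

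The cost is a revised sheet, a short outcome definition and blinded reclassification of earlier events. One limit should be acknowledged: Table 3 schedules blood counts at enrolment, on days 1, 2, 3, 5 and 7, and at ICU discharge. Reclassification of bleeds between those points, or after ICU discharge, will lean mainly on the AE/SAE records and on transfusion data where they exist.

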### Plans to promote participant retention and complete follow-up

It is not applicable because participation by the patient is only required while in the ICU. Data will be recorded upon enrollment and be followed up for 28 days. The detailed time points are listed in Table 3. The study period includes the screening period (D0, before enrollment), the intervention period (D1–D7), discharge from the ICU, and the 28-day follow-up period. The hospitalization and 28-day outcome require the hospital electronic information system or telephone-based follow-up strategy (questioning the patients or their family members over the phone). If the participants discontinue or deviate from intervention protocols, they will be encouraged to complete the follow-up of the study.

**Table 3 Tab3:** Study period

Time point	Enrollment	Intervention					Follow-up	Follow-up
	D0	D1	D2	D3	D5	D7	Discharge of ICU	D28
**Enrollment**								
Informed consent	✕							
Inclusion/exclusion	✕							
Randomization	✕							
**Intervention**								
UFH		✕	✕	✕	✕	✕		
Normal saline		✕	✕	✕	✕	✕		
**Assessment**								
Demographic data	✕							
Primary disease	✕							
Base condition	✕							
Blood routine	✕	✕	✕	✕	✕	✕	✕	
Serum chemistry examinations^a^	✕	✕	✕	✕	✕	✕	✕	
Coagulation function^b^	✕	✕	✕	✕	✕	✕	✕	
Inflammation index (PCT, CRP)		✕		✕		✕		
Blood gas	✕	✕	✕	✕	✕	✕	✕	
SOFA score		✕	✕	✕	✕	✕	✕	
APACHE II score		✕	✕	✕	✕	✕	✕	
ISTH score	✕	✕	✕	✕	✕	✕	✕	
JAAM score	✕	✕	✕	✕	✕	✕	✕	
Mechanical ventilation	✕	✕	✕	✕	✕	✕	✕	✕
CRRT	✕	✕	✕	✕	✕	✕	✕	✕
Duration in ICU							✕	
Outcome							✕	✕
AEs/SAEs		✕	✕	✕	✕	✕	✕	✕

*ICU*, intensive care unit; *UFH*, unfractionated heparin; *SOFA*, Sequential Organ Failure Assessment; *APACHE II*, Acute Physiology and Chronic Health Evaluation II; *ISTH*, International Society on Thrombosis and Hemostasis; *JAAM*, Japanese Association for Acute Medicine; *CRRT*, continuous renal replacement therapy; *AEs*, adverse events; *SAE*, severe adverse events

^a^Serum chemistry includes ALT, AST, TBIL, ALB, Pre-ALB, Scr, BUN, BNP, and cytokines

^b^Coagulation indices include PT, INR, APTT, Fibrinogen, D-D, FDP, and AT-III

### Sample size calculation

The sample size calculation was based on a previous study [18]. With a significance level of 0.1, test power of 80%, mortality of severe sepsis in the control group of 42.1%, mortality in the heparin group of 31.7%, and a 12% dropout rate, a total of 600 participants (300 in each group) will be needed.

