### Data analysis

Data will be described as the mean and SD or median and IQR according to the data distribution. The frequency of ICU mortality per group with a risk difference and 95% CI and a corresponding OR and 95% CI will be reported. Kaplan–Meier analysis will be used to analyze the rate of death in a time-to-event analysis, and the survival difference will be tested using a Cox proportional hazards model. For univariate analysis, the difference will be compared between the UFH and placebo groups using the Mann–Whitney U test or 𝜒2 and Fisher’s exact test. A two-tailed *p* value <0.05 was considered statistically significant. All statistical analyses were conducted using SPSS 22.0 and GraphPad Prism 9.0 software (GraphPad Software, San Diego, CA). The register number, participants lost due to follow-up, and violations of the protocols will be reported. The missing data will be handled with multiple imputation method.

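### The trial is sized at a significance level of 0.1 but tested at two-tailed 0.05, so the stated 80% power is really about 70% (75% with no losses)

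*Protocol article*

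**What the plan says.** The Sample size calculation section of the protocol article gives these inputs:

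- level and power: "With a significance level of 0.1, test power of 80" per cent;
- control arm: "mortality of severe sepsis in the control group of 42.1" per cent;
- heparin arm: "mortality in the heparin group of 31.7" per cent;
- losses: "a 12% dropout rate".

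The result is 600 participants, 300 per group. The section does not say whether the 0.1 is one-sided or two-sided.

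The Data analysis section gives the only decision rule in the article: "A two-tailed *p* value <0.05 was considered statistically significant". For the primary outcome it adds: "The frequency of ICU mortality per group with a risk difference and 95% CI and a corresponding OR and 95% CI will be reported". A 95% interval corresponds to a two-sided test at 0.05. No section says that the primary comparison is one-sided, or that it has a level of its own at 0.10.

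**The concern.** Power belongs to a particular test at a particular level. If the sample size is worked out at one level and the result is judged at a stricter one, the quoted power describes a test that will not be done.

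Two things are at stake. First, the chance of missing the assumed mortality benefit is larger than the protocol says, so a null result could be read as coming from an 80%-powered trial when it did not. Second, the protocol contains two thresholds for its primary outcome. A p value between 0.05 and 0.10 would count as positive at the level used for sizing and negative at the level used for analysis.

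**Working it through.** **Inputs.** From the Sample size calculation section: p1 = 0.421, p2 = 0.317, power 80%, dropout 12%, 300 per arm. From the Data analysis section: two-sided level 0.05. Allocation is 1:1 (Study design) and the primary outcome is the binary ICU mortality (Outcomes).

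Derived quantities:

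- difference d = 0.421 − 0.317 = 0.104, so d² = 0.010816;
- V = p1(1 − p1) + p2(1 − p2) = 0.243759 + 0.216511 = 0.460270;
- mean rate p̄ = 0.369, so 2p̄(1 − p̄) = 0.465678;
- evaluable per arm after dropout = 300 × 0.88 = 264.

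**Step 1: reproduce the 600.** The normal-approximation formulas per arm are

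- unpooled: n = (zα + zβ)² V / d²;
- pooled: n = [zα √(2p̄(1 − p̄)) + zβ √V]² / d²;

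with zβ = 0.8416 for 80% power. Each result is divided by 0.88 for dropout.

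| Level | zα | n per arm (unpooled, pooled) | after ÷ 0.88 | total, with rounding up |
|---|---|---|---|---|
| two-sided 0.10 | 1.6449 | 263.1, 265.1 | 299.0, 301.3 | 600 to 606 |
| two-sided 0.05 | 1.9600 | 334.0, 336.7 | 379.6, 382.7 | about 760 to 766 |
| one-sided 0.10 | 1.2816 | 191.8, 193.2 | 218.0, 219.5 | about 436 to 442 |

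For example, unpooled at two-sided 0.10: (1.6449 + 0.8416)² = 6.1826, and 6.1826 × 0.460270 / 0.010816 = 263.1. Rounded up to 264 and divided by 0.88, this is exactly 300 per arm.

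The totals vary by a few patients according to formula and to whether n is rounded up before or after the dropout step. Only the first row matches 600. One-sided 0.05 uses the same zα of 1.6449 and cannot be told apart numerically. So the 0.1 is not a misprint for two-sided 0.05, and it was not applied as a true one-sided 0.10.

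**Step 2: power at the level used for analysis.** Power = Φ{[d − zα √(2p̄(1 − p̄)/n)] / √(V/n)}.

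- n = 264, two-sided 0.10: [0.104 − 1.6449 × 0.04200] / 0.04175 = 0.836, power 79.8%. This recovers the stated 80%.
- n = 264, two-sided 0.05: [0.104 − 1.9600 × 0.04200] / 0.04175 = 0.519, power **69.8%**.
- n = 300, two-sided 0.05: [0.104 − 1.9600 × 0.03940] / 0.03917 = 0.684, power **75.3%**.

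Exact enumeration of the uncorrected chi-square test over the two binomial distributions gives 70.2% at 264 per arm and 75.2% at 300, so the approximation is not the cause. With a continuity correction the figures fall to 66.6% and 72.5%.

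**Step 3: what 600 patients can detect at 0.05.** Hold the control rate at 42.1% and solve the same expression for 80% power:

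- 264 per arm: 42.1% against 30.4%, a difference of 11.7 points;
- 300 per arm: 42.1% against 31.1%, a difference of 11.0 points.

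The assumed difference is 10.4 points.

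**The case against.** The strongest reply is that 70% is the pessimistic end. It treats all 12% of dropouts as contributing nothing. ICU mortality should be known for most patients, the protocol encourages those who stop treatment to complete follow-up, and missing data are to be multiply imputed. The effective number may then be nearer 300 than 264 per arm, with power near 75%. This is fair and the range should be given. However, 264 per arm is the protocol's own planning basis, and 75.3% is still short of 80%.

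A second reply is that sidedness is not stated. The hypothesis in the Discussion is directional, so the authors may have meant one-sided 0.05. That also reproduces 600, but it conflicts with the two-tailed rule in the Data analysis section. It moves the contradiction without removing it.

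Third, the arithmetic of the sample size section is correct for the level it states. That is true: the fault lies between the two sections, not within the first.

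Fourth, the harm is bounded. The stricter level governs the analysis, so the type I error is not inflated and a positive result at 0.05 is not weakened. The planned 95% interval will also show the imprecision of a null result. Both points stand, but they do not make the power claim correct.

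**Conclusion.** The concern holds. The stated 80% power applies to a two-sided 0.10 test (or its numerical equivalent, one-sided 0.05), and the protocol specifies a two-tailed 0.05 test. For that test, power is 69.8% after the planned 12% dropout and 75.3% if all 600 patients are analysed. The chance of missing the assumed effect is therefore about 30%, or about 25% with no losses, instead of 20%. Under either assumption about losses the protocol is wrong as written on a design property of its primary outcome.

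These figures rest on the protocol's own event rates, equal allocation and an uncorrected two-proportion test.

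**What to change.** Keep the two-sided 0.05 test and the 95% intervals, and make the Sample size calculation section agree with them. It should no longer give 0.1 as the trial's significance level. Suggested content: at a two-sided level of 0.05, 600 patients give about 70% power for 42.1% against 31.7% after 12% dropout (75% if all randomised patients are analysed), or 80% power for a difference of 11.7 points (11.0 if all are analysed).

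Recruitment opened in April 2018, so the amendment record should say that 600 was derived at 0.10. That keeps the history of the design clear. The change should be made before unblinding, so that only one threshold is in force when the primary result is seen.

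The cost is one sentence and a less favourable power figure, with no extra patients. If the sponsor wants to retain 80% power for the 10.4-point difference at 0.05, the alternative is a total of about 760 to 766 patients.

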### Data collection and management

Upon enrollment, baseline data, including epidemiologic characteristics, underlying disease, main diagnosis, Acute Physiology and Chronic Health Evaluation (APACHE II), SOFA, JAAM, and ISTH scores, infection sources and pathogens, and organ function indices, will be collected. General vital signs, infection indices (white cell count, neutrophil count, lymphocyte count, procalcitonin, C reactive protein, cytokines), organ function indices (cardiac, respiratory, hepatic, renal), coagulation variables (platelet counts, PT, INR, aPTT, fibrinogen, D-dimer, FDP, and antithrombin-III), and blood gas analyses will be recorded on the first, second, third, fifth and seventh days. Beyond that, treatment, including the volume of crystals, colloids, albumin and blood transfusion products, and urine volume, will be recorded every day. Outcomes, including ICU mortality, ventilator time, AEs/SAEs, and a follow-up visit on the 28th day, will be included.

All the data will be collected from the clinical electronic information system and recorded in the case report format (CRF). The data in the CRF recorded by researchers should be accurate, complete, and timely under the supervision and audit of two independent inspectors from the clinical research organization (CRO). All the CRFs will be recorded in an electronic document for statistical analysis. All participant centers were qualified by the National Medical Products Administration. The involved researchers complied with the Good Clinical Practice (GCP) guidelines during the study. All original documents will be stored in a locked site with restricted access at the Department of Critical Care Medicine of the First Affiliated Hospital of China Medical University for 10 years. The participant will be referred to by the participant code instead of the name in all the trial documents. Access will be granted to authorized person and the regulatory authorities to permit trial monitoring, audits, and reports.

